## Abstract

**Background:**

Overweight and obesity are considered to be serious public health problems. In pediatric populations, insulin resistance, dyslipidemia, and hypertension associated with obesity occur with increased frequencies. Metformin is an oral anti-hyperglycemic agent that has been demonstrated to be efficacious in the treatment of diabetic and non-diabetic obese adults. A considerable amount of pharmacogenetic research has demonstrated that genetic variation is one of the major factors affecting metformin response. Additionally, potential microbiota-mediated mechanisms of metformin effect have been recently described. However, scant work has been conducted in children, with no attention being paid to the potential effects of pubertal development. Thus, the main objective of the present study is to evaluate the effect of metformin treatment together with lifestyle recommendations in a randomized control trial (RCT) of obese children according to pubertal stage, genetic variants and signature of gut microbiota.

**Methods/design:**

This is a randomized, prospective, double-blind, placebo-controlled, multicenter trial, which is stratified by puberty and sex. Eighty pre-pubertal (40 boys and 40 girls) and 80 pubertal non-diabetic obese children (40 boys and 40 girls) are being recruited in four Spanish Clinical Hospitals. The inclusion criteria to participate in the RCT include a Body Mass Index (BMI) above the 95th percentile and age 7–14 years. The pubertal stage is determined based on the Tanner criteria. Participants are assigned to two groups in accordance with a randomization schedule and receive 1 g of metformin or placebo for six months in combination with healthy lifestyle recommendations in both groups. The primary outcomes include changes in the BMI Z score and the biomarkers associated with the early appearance of insulin resistance syndrome, inflammation, cardiovascular risk according of the presence of genetic determinants of metformin response, as well as possible modifications in microbiota.

**Discussion:**

This study will assess the differential response of metformin treatment at six months in pre-pubertal and pubertal obese children.

**Trial registration:**

Registered by European Clinical Trials Database (EudraCT, ID: 2010-023061-21) on 14 November 2011.

**Electronic supplementary material:**

The online version of this article (doi:10.1186/s13063-016-1403-4) contains supplementary material, which is available to authorized users.

## Background

The increased prevalence of obesity in pediatric populations is a public health problem [1]. Insulin resistance, impaired glucose tolerance, dyslipidemia, and hypertension are increased in children [2–4]. These metabolic alterations, which primarily result from obesity, begin in childhood and may manifest during adolescence or young adulthood, with diet and a sedentary lifestyle playing decisive roles [5]. In addition to a lifestyle intervention program, pharmacological treatments have been explored. Several drugs have been approved by the Food and Drug Administration (FDA) for the treatment of adult obesity. Currently, orlistat and sibutramine remain widely used in clinical practice in adults. Only orlistat has been approved for use in adolescents [6].

Metformin is an oral anti-hyperglycemic agent approved by the FDA to treat type 2 diabetes (T2D) in adults and children older than 10 years of age. Significant weight loss induced by metformin treatment has been demonstrated in both diabetic and non-diabetic obese adult patients [7]. In contrast, there is insufficient evidence regarding the effects of metformin in pediatric obesity. Several clinical trials have identified modest improvements following metformin treatment in insulin sensitivity in obese children with normal glucose tolerance [8–10], as well as a decrease in the BMI of obese adolescents [11]. In addition, metformin appears to improve lipid profiles in obese children [12, 13]. However, little is known regarding the effects of metformin, along with diet and exercise, on other measures associated with cardiovascular risk and inflammatory biomarkers. Six studies have evaluated the effects of doses of between 1000 and 2000 mg/day for 3–36 months in obese children and/or adolescents on inflammatory biomarkers related to obesity [10, 14–18]. These studies identified promising results, but did not follow a homogeneous distribution according to pubertal stage. Puberty is a very relevant confounding factor with a potential influence on insulin resistance development. Thus, randomized control trials (RCTs) with adequate statistical power appear necessary to enable the examination of these potential confounders [19], apart from a methodology based on a completely homogeneous distribution of factors, such as puberty and sex.

Furthermore, the composition of gut microbiota during early life has been proposed to influence the development of obesity and metabolic disease in children [20]. The scientific community emphasizes the need to disentangle gut microbiota signatures of specific human diseases from medication treatment success. Interestingly, the microbial mediation of the therapeutic effects of metformin through short-chain fatty acid production, as well as the potential microbiota-mediated mechanisms behind known intestinal adverse effects in the form of a relative increase in the abundance of *Escherichia* species have been demonstrated [21].

On the other hand, studies have shown variability in the therapeutic response of metformin treatment in T2D or obese patients. Variations in metformin response may reflect phenotypic differences in drug action or drug distribution. Genetic polymorphisms in drug uptake transporter genes have been increasingly recognized as a possible mechanism accounting for variation in drug response [22–24]. Therefore, the inclusion of genetic analyses in RCTs could be determinant to elucidate the variations in metformin response.

## Methods

### Objectives

In accordance with the previously discussed background, the present study has four main objectives: the first objective is to determine the efficacy of metformin in combination with a lifestyle intervention in reducing BMI in obese children compared with placebo after 6 months; the second objective is to evaluate the effects on insulin resistance inherent to metabolic syndrome; the third objective is to identify its effects on inflammatory, cardiovascular risk and oxidative stress biomarkers; the fourth objective is to evaluate the change of gut microbiota composition after treatment. Additionally, metformin differential response will be analyzed according to genetic polymorphisms in drug uptake transporter genes.

### Study design

The study is a multicenter investigation, stratified by sex and puberty (40 pre-pubertal girls, 40 pre-pubertal boys, 40 pubertal girls, and 40 pubertal boys). The patient distribution among groups is indicated in Fig. 1. The pubertal stage is determined based on the Tanner criteria [25]. This randomized, prospective, double-blind, placebo-controlled, multicenter trial is being conducted at four Spanish Hospitals: Córdoba, Granada, Santiago de Compostela and Zaragoza (Table 1).

**Fig. 1 Fig1:**
[figure not shown]
Participant flow diagram. *PPG* pre-pubertal girls; *PPB* pre-pubertal boys; *PG* pubertal girls; *PB* pubertal boys

**Table 1 Tab1:** Distribution of patients according to center

Hospital	Total (160)
Reina Sofía (Córdoba)	20 pre-pubertal girls
	20 pre-pubertal boys
Virgen de las Nieves (Granada)	10 pre-pubertal girls
	10 pre-pubertal boys
	10 pubertal girls
	10 pubertal boys
Clínico Universitario (Santiago de Compostela)	10 pre-pubertal girls
	10 pre-pubertal boys
	10 pubertal girls
	10 pubertal boys
Lozano Blesa (Zaragoza)	20 pubertal girls
	20 pubertal boys

Children are randomly assigned to receive metformin or placebo for six months. Both treatments are administered during meals (to minimize gastrointestinal side effects and the risk of hypoglycemia). The participants’ parents are given a coded vial of pills that contains either metformin or placebo pills for two months. The concealed allocation process ensures that the participants and all investigators are unaware of the allocated treatment. All participants are offered lifestyle intervention advice at all visits.

The clinical hospitals that participate in the RCT form part of the Maternal and Child Health and Development (SAMID network). Moreover, the RCT has been registered in the European Clinical Trials Database on 14 November 2011 (EudraCT, ID: 2010-023061-21).

In accordance with the “International Conference on Harmonization of Technical Requirements for Registration of Pharmaceuticals for Human Use” Guide (ICH): “CPMP/ICH/291/96 Note for Guidance on General Considerations for Clinical Trials,” this is a phase III clinical trial because it involves a commercialized drug for which a new indication that is not included in its technical specifications will be investigated.

The CONSORT statement (Consolidated Standards of Reporting Trials) has been taken into account in the study design report, as well as for the abstract and the flow diagram (Fig. 1), thereby increasing the reporting quality for the RCT. Moreover, the Standard Protocol Items: Recommendations for Interventional Trials (SPIRIT) guidelines for this study protocol are attached in Additional file 1.

### Participants

The study subjects comprise patients referred from the Pediatric Endocrinology Unit of the corresponding study centers. Children are eligible for this RCT if they meet the inclusion criteria (Table 2). The data are collected in the pediatric outpatient clinics by dieticians. The data and samples are codified according to each center and subsequently centralized at the Institute of Nutrition and Food Technology “José Mataix” (INYTA) in Granada, Spain.

**Table 2 Tab2:** Inclusion and exclusion criteria

Inclusion criteria	Exclusion criteria
BMI greater than the 95th percentile based on the standards set by Cole et al*.* [26]	Does not meet the established age
Age 7–14 years	Any previous underlying disease
No underlying disease or a history of pathology	Use of medication with metabolic side effects, such as diuretics, β-blockers, β-adrenergics, or corticoids
No medical treatment regarding weight control in the previous 12 months	Cases of monogenic obesity
No participation in a previous trial	Children subjected to long periods of rest
	Did not sign the informed consent

*BMI* Body Mass Index

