### Adverse effects and co-medication

To assess the safety of metformin administration, the primary evaluation criteria are the absence of the adverse effects (AEs) described. The patients are assessed regarding all symptoms at each visit to identify potential AEs and the use of co-medication in the previous two months. A contact number is provided to enable enquiries regarding any symptom perceived as adverse. At this number, the patient is informed about what to do in the event of an adverse reaction. They are also requested to suspend the medication. The following information is recorded: description, date of onset and end date, severity, assessment of relation to the study medication, other suspect drug or device and action taken. Follow-up information should be provided as necessary. The prominent AEs are as follow: diarrhea, nausea, blood in the stools, headache, dizziness, general discomfort, sleepiness, cold or flu, pharyngitis, otitis, allergic episode, lactic acidosis, urea increment, hypercreatininemia, hypertransaminasemia and vitamin B_12_ deficiency, as well as any other symptoms reported by the participants. The relationships of the AEs to the study medication will be assessed by a qualified medical investigator.

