### Blood, urine and fecal sampling

General biochemical analyses are performed at the participating hospitals following internationally accepted protocols.

Blood samples are obtained for biochemical and hematological screening tests between 08.30 and 10.30. Three milliliters of blood are collected at the beginning and at the end of the trial. The blood is drawn via the antecubital vein. Peripheral white blood cells (buffy coat) are taken for deoxyribonucleic acid (DNA) extraction. Moreover, a 1-ml urine sample is obtained for oxidation marker analysis. Children should not eat for 12 hours before the sampling. All samples are collected and stored frozen by the research staff. The samples will be analyzed in the clinical laboratory of each hospital, as well as the INYTA.

In order to studying the childrens’ gut microbiota, 100–200 g of fecal sample is collected in a sterile container by parents at the beginning and at the end of the trial. Immediately, all samples are stored frozen until to be analyzed at the INYTA.

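### Recent antibiotic use is not limited before stool sampling or used in the microbiota comparisons: this adds noise between arms and can bias the time and puberty comparisons

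*Protocol article*

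**What the plan says.** The Objectives section of the protocol article lists four main objectives and states that "the fourth objective is to evaluate the change of gut microbiota composition after treatment".

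Table 2 (Participants) has two criteria on drugs or treatment. One excludes "Use of medication with metabolic side effects, such as diuretics, β-blockers, β-adrenergics, or corticoids". The other requires "No medical treatment regarding weight control in the previous 12 months". Antibiotics are not mentioned there or elsewhere in the article.

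Under Blood, urine and fecal sampling, the "fecal sample is collected in a sterile container by parents at the beginning and at the end of the trial". A 12-hour fast is required before sampling, but no medication-free interval or deferral rule is given for the stool.

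Under Adverse effects and co-medication, children are assessed at each visit "to identify potential AEs and the use of co-medication in the previous two months". The adverse effects listed there include "sleepiness, cold or flu, pharyngitis, otitis, allergic episode".

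The Statistical analysis section compares relative abundances across times, treatments and puberty with the Mann-Whitney U test. No covariate, exclusion or sensitivity analysis for co-medication is attached to that comparison.

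**The concern.** Antibiotics act on bacteria, so a course shortly before a stool sample can be expected to alter what is measured. Under the stated criteria, a child who has just finished a course is eligible and can give the baseline stool straight away. Recovery over the next six months is then counted as change. A course shortly before month 6 has the opposite effect on the end sample. The article expects pharyngitis and otitis during the trial. If some of these are treated with antibiotics (an assumption; the article does not say), end samples are exposed too.

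At stake is the interpretation of the fourth objective. A shift from start to end could be partly antibiotic depletion or recovery. A difference between pubertal stages could partly reflect different exposure. The between-arm comparison would carry extra variability from a source that the trial already records but does not use.

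**Working it through.** The article gives no antibiotic rate and no figure on this point, so there is nothing to reproduce. The check sets the sections side by side, then sizes the exposure under declared assumptions.

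**1. Can an exposed sample enter?**
- Eligibility: the four drug classes named in Table 2 include no antibiotic. The exclusion for previous underlying disease does not naturally cover a short course for an acute infection.
- First-visit history: medication use appears there among pregnancy and neonatal items, so it is not a screen for recent antibiotics.
- Sampling: the stool is tied to the start and end of the trial only.
- Analysis: the co-medication record exists but is not linked to eligibility, stool timing or the microbiota tests.

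Nothing in the stated rules keeps an exposed sample out or marks it.

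**2. How many pairs?**
- Completers: 160 × (1 − 0.20) = 128, using the planned total and the 20% loss from the Sample size section.
- Assumed exposure before any one sample: p = 5-15%, independent at the two times.
- Share of pairs with at least one exposed sample: 1 − (1 − p)².
 - p = 0.05: 1 − 0.95² = 0.0975; × 128 = 12.5 pairs.
 - p = 0.15: 1 − 0.85² = 0.2775; × 128 = 35.5 pairs.
- Per arm-by-puberty group of 128 / 4 = 32: 3.1 to 8.9 pairs.

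**3. How uneven could the arms be by chance?**
The expected imbalance is zero. The standard error of the difference in exposed proportion is √(2q(1 − q)/n), with n per arm and q the proportion exposed. The range q = 10-30% is assumed and is close to the pair-level range in step 2. The last column was simulated from two binomial samples.

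| n per arm | q | SE | Chance of a difference of 10 points or more |
|---|---|---|---|
| 80 (all randomised) | 0.10 / 0.20 / 0.30 | 0.047 / 0.063 / 0.072 | 4.8% / 13.8% / 19.5% |
| 64 (all completers) | 0.10 / 0.20 / 0.30 | 0.053 / 0.071 / 0.081 | 5.5% / 15.1% / 20.9% |
| 40 (one pubertal stage) | 0.10 / 0.20 / 0.30 | 0.067 / 0.089 / 0.102 | 18.8% / 32.6% / 39.3% |
| 32 (one stage, completers) | 0.10 / 0.20 / 0.30 | 0.075 / 0.100 / 0.115 | 14.2% / 27.1% / 33.9% |

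The chance is lower at 32 than at 40 because counts are whole numbers. Ten points is exactly 4 of 40, whereas with 32 per arm the smallest qualifying difference is 4 children, or 12.5 points.

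**4. Which comparisons are protected?**
- *Treatments:* randomised, half of the children at each centre per arm, so protected in expectation. What remains is noise and the chance imbalance in step 3.
- *Times:* not randomised. Recovery or depletion can appear as change in either arm.
- *Puberty:* not randomised and partly tied to centre. In Table 1, Córdoba enrols only pre-pubertal children (40 of 80) and Zaragoza only pubertal children (40 of 80). Any difference in antibiotic use by age or city would enter this comparison directly. The article gives no evidence that such a difference exists.

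**The case against.** The strongest reply is that the trial is randomised, double-blind and placebo-controlled. Antibiotic exposure is balanced in expectation, and the placebo arm shows any recovery or depletion unrelated to metformin. This stands for the treatment contrast, including within a pubertal stage. A reader might infer that the measured metformin effect on the microbiota is biased by antibiotics. The document does not support that.

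A second reply is that a journal article condenses, and that stool instructions or the use of co-medication may sit in the full protocol or the analysis plan. For the analysis part this has force, and silence there would not be a finding alone. It has less force for Table 2 and the sampling rule, which the article sets out. An analysis plan also cannot change when a stool sample was taken.

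Third, the rate is assumed. The count in the working shows how many pairs are exposed, not how far abundances shift or how much power is lost. That is correct, and no bias or variance inflation is claimed.

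Fourth, a reader might take the Background remark on "the need to disentangle gut microbiota signatures of specific human diseases from medication treatment success" as a commitment to control for other drugs. It is followed by a discussion of metformin and does not mention antibiotics, so the point does not rest on it.

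Finally, one might want to drop exposed pairs from the main analysis. Antibiotic use before month 6 arises after randomisation and could differ by arm. Excluding on it would weaken the randomised comparison, so it should not be the main analysis.

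**Conclusion.** The point holds in a limited form. Followed as written, the plan admits stool samples taken soon after antibiotics into a main objective and does not use the record that would identify them. In the metformin-placebo contrast the consequence is added noise and chance imbalance. Bias is possible in the comparisons across times and by puberty. Neither its presence nor its direction can be established from the document.

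The size is about 12-36 of 128 pairs with an exposed sample, if 5-15% of children are exposed before each sample, independently, and 20% are lost. With 10-30% of children exposed, a chance difference of at least 10 points between arms has a probability of about 5-21% among all completers and 14-34% among completers in one pubertal stage. The point also assumes that antibiotics in the preceding two months matter for the sample. That window is chosen because it is already recorded, not because the article justifies it.

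The principal variable, BMI Z score, is untouched. This is a cheap improvement to a main but non-principal objective and does not threaten the trial's primary result.

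**What to change.** 1. **Baseline stool, children still to be recruited.** Add to the stool-sampling section that the baseline sample is taken before randomisation and first dose, and is deferred if the child took antibiotics in the preceding two months. Confirm that the co-medication question is asked at the baseline visit as well.
2. **Exposure flag, all children.** From the co-medication record, flag antibiotic and probiotic use in the two months before each stool sample, and report the flags by arm and pubertal stage.
3. **Analysis.** Keep all pairs as the main between-arm microbiota comparison and report unflagged pairs as a sensitivity analysis. Read changes over time against placebo, not within one arm alone. Interpret the puberty comparison with the flag counts beside it.

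Cost: an amendment while recruitment continues, a short wait for some children, and one variable derived from data already collected. Baseline samples taken before the change were collected without the rule, so earlier and later children differ in this respect. The flag allows that to be described but does not undo it.

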### Randomization

The participants are assigned to metformin or placebo in accordance with a randomization schedule generated by the Pharmacy Service of the Virgen de las Nieves University Hospital in Granada, with MAS 100 version 2.1 software (Glaxo-Welcome, Madrid, Spain) by the Support Consortium to Biomedical Research Network (CAIBER). At each center, 50 % of the children are assigned to each group.

The drug presentation format for the metformin and placebo groups has the same appearance. The local physician responsible for the procedure is only aware of the box/bottle codes of the tablets (as well as the registration number of the participating child). These codes have a corresponding equivalent available only to the coordinating investigator who has the other data of pharmaceutical interest, such as the origin, lot number and manufacturing and packaging dates (as well as whether the drug is metformin or placebo). The aforementioned local physician is not aware of these data and thus assigns the participant to one study group, without knowledge of the primary treatment administered.

### Breaking of the study blind

All research staff are blinded for both the treatment allocation during the time of the study and the data analysis. The study blind will be broken after all analyses are completed. In the case of emergencies (e.g., serious adverse events, potentially unexpected serious adverse reactions), the blind will be broken following consultation with the principal investigator. These events will subsequently be reported to the Medical Ethics Committee.

### Interventions

The patients are instructed to taking a initial dose of 50 mg twice daily for 10 days, followed by 500 mg twice daily until the end of the treatment. The presentation comprises tablets in opaque, white plastic containers and a side label with 28 units. The dietician centers administer a food frequency questionnaire (FFQ) and a physical activity survey to all participants at the beginning and at the end of the trial. All participants are provided with standardized healthy lifestyle advice at the start of a one-on-one session, including a healthy diet and exercise advice sheet. The participants attend an initial trial baseline visit, followed by three additional visits at 2-month intervals (Fig. 2), which include anthropometric parameter and blood pressure (BP) assessments, as well as a physical examination. A medical history is obtained for each participant, including documentation of the family history.

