**Fig. 2 Fig2:**
[figure not shown]
Activity schedule that may occur during each contact with the participant

To ensure the traceability of the treatments, a systematic record of the name of the pharmaceutical preparation, and the quantity and lot number dispensed to each subject are maintained in the corresponding data collection book. The data are updated according to the standard working procedures (SWPs) for the preparation and control of 500-mg metformin tablets and according to the SWPs for the control of pills, which are provided by the Hospital Pharmacy Department.

At the first visit, an extensive history is obtained. The duration of pregnancy, birth weight, neonatal feeding, use of medication, tobacco and alcohol, and the presence of maternal gestational diabetes are reported. Regarding family history, data on hypertension, obesity, hypercholesterolemia, cardiovascular disease, and *diabetes mellitus* in first-degree (parents) and second-degree (grandparents) family members are collected. Girls are asked whether and when they experienced menarche. The parental education level is recorded, as well as height and weight.

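### The written starting dose of 50 mg does not fit the only tablet strength the protocol names (500 mg), and the predicted pill count for the first 10 days is ambiguous as a result

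*Protocol article*

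**What the plan says.** All references are to the protocol article.

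- **Dose (Interventions).** Patients take "a initial dose of 50 mg twice daily for 10 days, followed by 500 mg twice daily until the end of the treatment".
- **Tablet strength (Interventions, paragraph on traceability).** Working procedures are cited "for the preparation and control of 500-mg metformin tablets". No other strength appears in the article.
- **Container (Interventions).** The product is supplied as "tablets in opaque, white plastic containers and a side label with 28 units".
- **Supply (Study design).** Parents receive "a coded vial of pills that contains either metformin or placebo pills for two months". Interventions sets the follow-up visits two months apart.
- **Abstract (Methods/design).** Children "receive 1 g of metformin or placebo for six months".
- **Use of the pill count (Adherence and tolerance; Statistical analysis).** Adherence is a percentage with pills predicted as its denominator, and it enters the linear mixed model as a fixed effect. Tolerance is to be summarised against the dose level reached.

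**The concern.** The dosing sentence is an operative instruction for children aged 7 to 14, and its first step cannot be given in whole units of the only product described. Randomization says that the metformin and placebo presentations look the same, but it mentions no second strength. A reader therefore cannot tell what a child takes in the first 10 days.

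Three things depend on the answer:

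- the early exposure against which tolerance is to be summarised;
- the number of tablets a family should have used by the first follow-up visit;
- the denominator of the adherence term in the main model.

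Trial status says that recruitment continues, so a correction can still take effect.

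**Working it through.** **Inputs from the article**

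- Starting step: 50 mg, twice daily, 10 days, hence 2 × 10 = 20 intakes (Interventions).
- Main phase: 500 mg twice daily (Interventions).
- Named tablet strength: 500 mg (Interventions).
- Container: 28 units (Interventions).
- Supply interval: two months (Study design; visit spacing in Interventions).

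**Assumptions.** The article does not give its months in days. I take two months as 56 to 62 days, with 60 for illustration, and six months as 182 days.

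**1. The plan's own figure.** Main-phase daily dose = 2 × 500 mg = 1000 mg = 1 g. This reproduces the abstract, so the main phase is consistent with the named tablet.

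**2. Starting step against tablet strength.** Tablets per intake = 50 / 500 = 0.1. Daily dose as written = 2 × 50 = 100 mg, one tenth of the 1000 mg that whole 500-mg tablets twice daily would deliver.

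**3. Container against interval.**

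- Days covered by 28 units at two a day: 28 / 2 = 14.
- If the first 20 intakes were each a tenth of a tablet, they would use 20 × 0.1 = 2 tablets. One container would then last 10 + (28 − 2)/2 = 23 days.
- Tablets per interval at one per intake: 2 × 56 = 112 to 2 × 62 = 124.
- Containers per interval: 112/28 = 4.0 to 124/28 = 4.4.

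**4. Pills predicted under three readings of the first 10 days**

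| Reading | First 60 days | 182 days |
|---|---|---|
| Every intake is one tablet, including 20 low-strength ones | 2 × 60 = 120 | 2 × 182 = 364 |
| First 20 intakes are each a tenth of a 500-mg tablet | 2 × 50 + 2 = 102 | 2 × 172 + 2 = 346 |
| Only 500-mg tablets from day 11 are counted | 2 × 50 = 100 | 2 × 172 = 344 |

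The spread is 18 to 20 pills. That is 18/120 = 15% to 20/120 = 17% in the first 60 days, and 18/364 = 4.9% to 20/364 = 5.5% over 182 days.

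**5. What this does to the model.** If everyone is given the same denominator, changing it only rescales adherence. With adherence entered as a linear term, the treatment estimates would not move. The ambiguity matters for those estimates only if the denominator is set differently for different children or centres, or if adherence is compared with a cut-off.

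**The case against.** The strongest reply is that this is a condensed article. The traceability paragraph cites procedures for 500-mg tablets but does not say that nothing else is prepared, so the pharmacy may supply a second strength that the article omits. This cannot be ruled out, and the finding is therefore a contradiction to be resolved, not proof of a dosing error. It does not remove the mismatch, because the article states both figures and offers nothing to connect them.

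A reader might infer more than the document supports:

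- **That the regimen cannot be dispensed.** At most this applies to the 10-day step, and only with whole 500-mg tablets. The main phase can be supplied as written.
- **That the abstract contradicts the dosing section.** Its 1 g equals 2 × 500 mg. Leaving out a 10-day lead-in is ordinary condensation.
- **That families receive only 28 tablets for two months.** This requires the vial to be a single 28-unit container. Interventions speaks of containers and the Discussion of bottles, both plural, so several per visit are possible. Four would cover exactly 4 × 28 / 2 = 56 days. The number per visit is a detail an article may leave to the full protocol.
- **That the predicted pill count is undefined.** It is two a day from day 11. Only the first 20 intakes are in doubt, and the full protocol may state the number.
- **That centres dosed children differently.** Nothing shows this. The article gives one instruction for all patients, half the children at each center go to each arm, and the model adjusts for center. No effect on the six-month comparison is demonstrated.

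**Conclusion.** The concern holds in a narrow form. The written starting dose and the only named tablet strength differ by a factor of ten, and the article gives no means of delivering the smaller amount. Because this is a dosing instruction for children, it needs correcting even if one of the figures proves to be a misprint. The document does not settle which statement is wrong.

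The supply wording and the pill count are secondary and would be minor on their own. The first is an ambiguity about how many containers make up a two-month supply. The second is an uncertainty of at most 20 pills, about 5% over six months and 15 to 17% in the first two months. These sizes rest on the assumed lengths of two and six months and on two intakes a day throughout.

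**What to change.** 1. Reconcile the Interventions, Study design and Adherence and tolerance sections with the approved protocol and the pharmacy procedures. The result should be one consistent statement of the starting step, the tablet strength or strengths supplied, the units per container and the containers per two-month visit.
2. Check the dispensing records for what was actually supplied for the first 10 days. Interventions says that the preparation, quantity and lot number are recorded for each subject, so the information should exist.
3. Correct whichever statement proves to be in error. No dose is proposed here.
4. Derive pills predicted from the reconciled regimen, state how the first 20 intakes are counted, and apply the same rule to every child.

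The cost is a document correction and a check of existing records. The sample size and the form of the statistical model do not change.
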